
In the current context, the verification of the correct placement of the nasogastric tube is carried out through a rigorous multidisciplinary protocol. The procedure involves the aspiration of at least 5 ml of gastric secretion and the subsequent evaluation by pH test. In case of the procedure being unsuccessful, the placement is defined through chest X-ray. Based on the collected data, the percentage of patients in whom it was possible to successfully apply this protocol was 42% of all placements performed. This result highlights a limited success rate, largely associated with intrinsic difficulties encountered during the aspiration phase. These difficulties are frequently linked to the current use of nasogastric tubes, demonstrating significant complexity in implementing the multidisciplinary protocol. The data aligns with current scientific literature, indicating potential limitations in the application of this procedure. This could not only compromise nutritional benefits for the patient but also hinder cost optimization from an economic sustainability perspective. To date, existing scientific literature lacks clinical studies addressing the highlighted issues, both in terms of overcoming difficulties in gastric aspiration and adopting the use of electronic pH meters [[38], [39], [40], [41], [42], [43], [44]].

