### Other outcomes of interest

1.4

Evaluation of cost reduction compared to the current gold standard (chest radiography). Costs related to the entire NGT placement procedure (cost of NGT, personnel, clinical procedure for monitoring correct placement) will be evaluated. This calculation will be expressed in Euros.

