### Study procedures

2.2

Participants will be enrolled in three study arms, assigned according to the defined randomization criterion, to evaluate three different NGT models along with the use of an electronic pH meter. The first NGT is the *NUTRICIA FLOCARE PUR TUBE CH14 double lumen*, which features an additional lumen to the nutritional lumen specifically for pH aspiration. The other two NGTs are the *INNOVAMEDICA single lumen CH10 AVANOS_ST CH10* and the *INNOVAMEDICA single lumen CH12 AVANOS_ST CH12*, which have a single lumen. In all three study arms, the determination of the correct positioning (primary outcome) will take place through the monitoring of the gastric pH (gastric aspirate 5 ml; pH value ≤ 5.5)^46^ through the use of an electronic pH meter (pH Strips & Reader Innovamedica model pH X-act) which will be compared with the CXR (current gold standard). The comparison with the CXR will allow to evaluate the sensitivity and specificity of the pH test. An important aspect of the study is the evaluation of the time efficiency in starting nutritional therapy. This is measured in minutes and aims to determine if the pH test can reduce the time taken for NGT positioning evaluation compared to the current 1440 min required for chest X-ray assessments. The time frame is obtained from the evaluation of the service at IRCSS Humanitas Research Hospital. Furthermore, Patient tolerance to the NGT will be assessed at 24, 48 72 h post-placement using the NRS scale. This will help identify pain levels and characteristics, to evaluate whether different NGT calibers (CH) affect patient tolerance. Throughout the entire period of hospitalization of the patient, complications associated with the positioning of the NGT will be recorded. These include mispositioning of the NGT (assessed by chest x-ray); tracheobronchial aspiration; aspiration pneumonia; lesions of the oesophageal mucosa and upper airways (assessed by clinical examination and instrumental tests requested by the attending physicians). During the post-clinical phase, an economic analysis will be conducted to evaluate potential cost savings from using the pH test for correct NGT positioning, with respect to X-ray use. This includes analysing costs of auxiliary personnel (based on transport times to radiology, calculated as Euro/hour), professional fees for performing chest Xrays, and the cost of the Xrays themselves. A graphical representation of the study procedures is depicted in Fig. 1.

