#### Clinical investigation intervention

2.2.5

*Medical device.* This randomized clinical trial will include three study arms to which patients will be assigned according to the enrolment criteria set out in the research protocol. Each arm of the study will involve a different type of NGT. The types of NGTs are reported in section 1.1. These two NGTs have a single lumen and are made of specific materials that give greater performance. In all three study arms, the determination of the correct positioning (primary outcome) will take place through the monitoring of the gastric pH (gastric aspirate 5 ml; pH value ≤ 5.5) through the use of an electronic pH meter (pH Strips & Reader pH X-act) which will be compared with the chest X-ray (current gold standard).

*Labelling and supply.* All electro medical equipment (pH meter) for this study will be provided free of charge for testing purposes by the respective manufacturers/suppliers, while medical devices (NGTs) will be provided free of charge.

*Storage conditions.* The NGT devices can be kept in the common storage environments used for the principals. A total of two pH metres will be assigned to each ward. The management and storage of the device will be carried out by the analysis laboratory of the structure in which the trial is being performed.

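### The cost outcome is set against chest radiography, although the hospital's current pathway is pH test first with X-ray only on failure; at the plan's own rates this can overstate the X-rays saved about threefold

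*Protocol article*

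**What the plan says.** Section 1.4 (Other outcomes of interest) states the cost outcome as "Evaluation of cost reduction compared to the current gold standard (chest radiography"), and defines its scope broadly: "Costs related to the entire NGT placement procedure (cost of NGT, personnel, clinical procedure for monitoring correct placement) will be evaluated", in Euros.

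Section 2.2 (Study procedures) describes the analysis: "an economic analysis will be conducted to evaluate potential cost savings from using the pH test for correct NGT positioning, with respect to X-ray use". It then lists what is costed: "This includes analysing costs of auxiliary personnel (based on transport times to radiology, calculated as Euro/hour), professional fees for performing chest Xrays, and the cost" for each X-ray.

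Section 1 (Introduction) describes how placement is verified at the hospital now: "The procedure involves the aspiration of at least 5 ml of gastric secretion and the subsequent evaluation by pH test", and then "In case of the procedure being unsuccessful, the placement is defined through chest X-ray". It reports that this pathway could be applied successfully in 42% of placements. Section 2.5.1 uses the same 42% as the standard-method rate and 62% as the rate to be shown for the study tubes.

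Three further statements bear on the point. Under section 1.5, every placement in the trial gets both a pH test and a chest X-ray. Under section 2.2.5, the pH meters are supplied free, "while medical devices (NGTs) will be provided free of charge". Section 3 says that a reading above pH 5.5 is an indication for X-ray confirmation.

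**The concern.** The article works with two different versions of current practice. For efficacy, current practice is the pH-first pathway, credited with 42% success. For cost, current practice appears to be chest radiography, which on its natural reading is credited with no successful pH checks at all. A saving calculated that way credits the study tubes with X-rays the hospital already avoids.

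The trial data cannot correct this. All three arms use study tubes, so there is no arm with the tube now in use. Every placement is X-rayed, so observed X-ray use is the same in each arm. The saving is therefore a modelled figure, and the comparator named in the protocol largely decides it.

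A second, smaller problem is that the two descriptions of the cost items differ. Section 1.4 covers both sides of the comparison. The list in section 2.2 names only items that fall when an X-ray is avoided, and does not name the tube, strips, reader or aspiration time. Lower cost is one of the benefits put forward in the abstract, so what it is measured against matters to a reader.

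**Working it through.** **Inputs.** Current success rate of the pH-first pathway: 42% (Introduction; section 2.5.1). Target rate with the study tubes: 62% (section 2.5.1). Power 80%, type I error 5%, 47 patients per arm (section 2.5.1). The article gives no unit costs.

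**Step 1: is 42% really the plan's benchmark for current practice?** The article states no cost figure, so the figure to reproduce is the sample size. A one-sample test of a proportion against a fixed 42%, two-sided, gives

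n = [1.960 × √(0.42 × 0.58) + 0.842 × √(0.62 × 0.38)]² / 0.20² = 47.3

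This matches the stated 47 (power at 47 is 79.7%). A two-sample comparison would need 97 per arm and a one-sided one-sample test about 37. The design therefore treats 42% as the fixed rate for current practice.

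**Step 2: X-rays per 100 placements.**

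- X-ray for all: 100
- Current pH-first pathway: 100 − 42 = 58
- Study tubes at the design rate: 100 − 62 = 38

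**Step 3: X-rays avoided by the study tubes.**

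- Against X-ray for all: 100 − 38 = 62
- Against current practice: 58 − 38 = 20
- Ratio: 62 / 20 = 3.1

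**Step 4: other rates for the study tubes.** With new rate p, the ratio is p / (p − 0.42).

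| New rate | Avoided per 100, against X-ray for all | Avoided per 100, against current practice | Ratio |
|---|---|---|---|
| 50% | 50 | 8 | 6.25 |
| 62% | 62 | 20 | 3.1 |
| 70% | 70 | 28 | 2.5 |
| 80% | 80 | 38 | 2.1 |
| 90% | 90 | 48 | 1.9 |

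**Step 5: readings above pH 5.5.** Steps 2 to 4 assume that each placement with a measurable pH avoids an X-ray. Section 3 says that high readings do not. If the same share of readings is high under both pathways, both counts shrink in proportion and the ratio stays at 3.1. If the 42% already means confirmed placements while the 62% means only measurable ones, the ratio rises. Assuming, for illustration, that 90% of readings are at or below 5.5, it is 0.62 × 0.90 = 0.558, so about 56 against about 14 (55.8 − 42 = 13.8), or 4.0.

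**Step 6: added device and staff cost.** Let e be the extra tube and pH-testing cost per placement, as a share of the cost of one X-ray pathway. This is an assumption, since no prices are given. The net saving against current practice is 0.20 − e: 0.15 at e = 0.05, 0.10 at e = 0.10, zero at e = 0.20 and −0.10 at e = 0.30. A calculation against X-ray for all that counted X-ray items only would show 0.62 throughout.

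**The case against.** The strongest reply is that nowhere does the article say every comparator placement will be costed with an X-ray. The wording in sections 1.4 and 2.2 could mean a per-check comparison of two confirmation methods, in line with the accuracy comparison, and section 3 speaks of avoiding X-ray more often, which is an incremental claim. This stands as a caution: X-ray-for-all is the natural reading, not a stated rule. It does not remove the problem, because neither section names the pathway the Introduction describes as current.

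Several stronger readings are tempting, and the documents do not support them:

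- **That the plan charges nothing for the new devices.** Section 1.4 commits to the tube, personnel and the monitoring procedure, and the list in section 2.2 opens with words that do not make it exhaustive. Free supply during the trial does not show that devices will be priced at zero; the source of prices may be set in the full protocol.
- **That X-rays still needed with the study tubes are left out.** The list in section 2.2 includes the cost of X-rays and does not restrict it to the comparator.
- **That the overstatement is five-fold (100 / 20).** This needs a strategy with no X-rays at all, which section 3 contradicts.
- **That the saving is certain to be greatly overstated in money.** Without unit costs, only the X-ray count can be compared.

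It is also fair that cost is only an other outcome of interest. It is outside the primary and secondary endpoints and the sample size, and section 3 leaves cost-effectiveness in diverse settings to later research. That limits the weight of the point but not its correctness.

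**Conclusion.** The point holds for the comparator. The cost outcome is set against chest radiography, while the article's own account of current practice is pH test first with X-ray fallback. At the design rates, costing the comparator as X-ray for all would credit the study tubes with 62 X-rays avoided per 100 placements instead of 20. That is about 3.1-fold, with a range of 1.9- to 6.25-fold for new-tube rates of 90% to 50%. The figure rests on three assumptions: the X-ray-for-all reading, every placement not confirmed by pH going to X-ray, and high pH readings being equally common under both pathways. It is a ratio of X-rays, not of euros.

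On cost items the finding is narrower. Sections 1.4 and 2.2 differ and need to be reconciled; the article does not show that device costs will be omitted. The sign of the net saving against current practice is open: it turns negative if the added cost per placement exceeds one fifth of an X-ray pathway.

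**What to change.** In sections 1.4 and 2.2:

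1. Name the main cost comparator as the hospital's current pathway: pH test first, with X-ray in the 58% of placements where it does not succeed.
2. For each study arm, count the X-rays that would still be needed under the pathway the article describes, that is, for placements without a 5 ml aspirate or with pH above 5.5. The safety X-rays done on every trial placement should not enter this count.
3. Align the list in section 2.2 with section 1.4, so that tube, strips, reader and staff time are costed, at ordinary prices although the tubes and meters are supplied free in the trial.
4. Keep X-ray-for-all only as a secondary scenario, labelled as such.

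The cost is a change of wording and a small costing model. Aspirate and pH results are already collected; ordinary device prices would have to be obtained. The downside is a less favourable stated saving. Randomisation, the primary endpoint and the sample size are unchanged.

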**Fig. 1 fig1:**
[figure not shown]
Sample enrollment and study Procedures **Legend.** NGT= nasogastric tube; CH=Charrier; NRS= numerical rating scale.

#### Recruitment of study participant

2.2.1

Over a time period of at least 6 months, patients admitted to the wards of IRCCS Humanitas Research Hospital will be subsequently enrolled in three study groups according to the inclusion/exclusion and randomization criteria described further on.

*Inclusion Criteria*: Eligibility criteria for a study involving NGT placement for enteral nutrition in hospitalized patients are as follows: Firstly, patients considered for NGT insertion should not have any current complications that may interfere with the placement of the tube, particularly those related to anatomical challenges or known risks associated with elective NGT placement. Secondly, only legally adult patients are eligible to participate. Finally, it is imperative that all participants consent to the use of their personal data for research purposes, which is formalized through the signing of a consent form. These criteria are essential to ensure the selection of suitable candidates for the study, minimizing potential complications and ensuring informed participation.

*Exclusion Criteria*: Patients who, at the time of positioning, present neurological complications such as to involve a significant alteration of the level of consciousness measured by the Glasgow Coma Scale (GLS) with a value ≤ 8 will be excluded. Patients who have contraindications to NGT placement, such as basal skull fractures; Maxillo facial disorders; Unstable cervical spinal injuries; Nasal/pharyngeal/oesophageal obstruction or ulceration; Choanal atresia; Tracheoesophageal fistula; Oesophageal/pharyngeal pouch; Oesophageal stricture or other abnormalities of the oesophagus; Oesophageal tumours or have undergone oesophageal surgery; Oropharyngeal tumours or have undergone oropharyngeal surgery; Post laryngectomy; Actively bleeding oesophageal or gastric varices; Gastric outflow obstruction; Intestinal obstruction; pregnant women.

#### Assignment to investigation groups

2.2.2

The randomization will be conducted using sealed envelopes prepared by a dedicated statistician for the study. Upon opening each envelope, a dual signature will be applied to ensure that the randomization procedure adheres to statistical requirements. The process will be managed to maintain confidentiality, and none of the professionals involved in the clinical procedures of the study will have access to randomization information. The study will employ a specially designed procedure to ensure the integrity and statistical validity of the randomization process.

#### Subject withdrawal procedures

2.2.3

The patient has the right to decide to abandon the study at any stage or to withdraw his consent by communicating the decision to the principal investigator or other investigator who will become reversible at each stage of the study.

#### Methods for minimizing bias

2.2.4

The pH measurement of the gastric aspirate, as indicated by several authors, will be evaluated at least 1 h after food intake. If the patient is taking antacids or proton pump inhibitors (PPI), we hypothesize that the pH data may present possible alterations; in this regard we will record variables of interest, reporting everything in the CRF form, including the intake of antacids and/or PPI drugs, daily dosage, and time since the last intake of the drug at moment of pH measurement. We believe the latter evaluations are necessary as to date there are no clear guidelines, protocols or clinical studies that highlight how to deal with such possible clinical biases. Furthermore, the calibration of the instrument will be carried out daily following the instructions and kit which are provided by the manufacturer by a responsible and trained healthcare professional. Additionally, before the start of the study, a specific 2-h training session will be conducted to train healthcare professionals on the study procedures and the use of the pH meter. This course will be delivered by a specialist nurse, a nutritionist, and by the clinical quality and risk department of the hospital.

#### Clinical investigation intervention

2.2.5

*Medical device.* This randomized clinical trial will include three study arms to which patients will be assigned according to the enrolment criteria set out in the research protocol. Each arm of the study will involve a different type of NGT. The types of NGTs are reported in section 1.1. These two NGTs have a single lumen and are made of specific materials that give greater performance. In all three study arms, the determination of the correct positioning (primary outcome) will take place through the monitoring of the gastric pH (gastric aspirate 5 ml; pH value ≤ 5.5) through the use of an electronic pH meter (pH Strips & Reader pH X-act) which will be compared with the chest X-ray (current gold standard).

*Labelling and supply.* All electro medical equipment (pH meter) for this study will be provided free of charge for testing purposes by the respective manufacturers/suppliers, while medical devices (NGTs) will be provided free of charge.

*Storage conditions.* The NGT devices can be kept in the common storage environments used for the principals. A total of two pH metres will be assigned to each ward. The management and storage of the device will be carried out by the analysis laboratory of the structure in which the trial is being performed.

#### Discontinuation or modifications of the intervention

2.2.6

Interruption of treatment foreseen in case of impossibility to carry out the NGT positioning procedure.

#### Compliance with clinical investigation intervention

2.2.7

Correct positioning will be monitored by pH testing with an electronic pH meter and chest X-ray. Any acute complications related to the positioning of the nutritional aid and the patient's tolerance during the period of hospitalization will also be monitored.

#### Clinical investigation specific preventive measures

2.2.8

The pH measurement of the gastric aspirate will be evaluated at least 1 h after food intake. If the patient is taking antacids or proton pump inhibitors (PPI), we hypothesize that the clinical data (pH test) may present possible alterations; in this regard we will evaluate as variables of interest, reporting everything in the CRF form, intake of antacids and/or PPI drugs, daily dosage and, when the pH is measured, time since the last intake of the drug. We believe the latter evaluations are necessary, since this data is a possible clinical bias and, in the literature, there are no clinical studies, protocols or guidelines that answer this question.

#### Concomitant treatments

2.2.9

It is important to consider pharmaceuticals or medicines or supplements or foods that can alter gastric pH prior to the procedure.

### Medical device accountability

2.3

This study does not include specific procurement or storage of materials (NGTs). With regard to the procurement and storage of electromedical devices to be used (electronic pH meters), a minimum supply of two instruments will be required which will be managed in compliance with the regulations in place at the IRCCS Humanitas Research Hospital Rozzano (MI), the Clinical Engineering service and according to the manufacturer's specifications. Based on the number of electronic pH meters supplied by the manufacturer, hospital departments will be assigned electromedical device (electronic pH meter and reagent strips) in order to carry out the tests.

### Return or destruction of the medical device

2.4

As regards the NGT in use, if they are removed after positioning during the hospitalization period, the disposal will be the responsibility of the hospital through the procedure that regulates special hospital waste. The pH meters in use, being supplied free of charge by the distributing company, will be returned at the end of this study.

### Statistical considerations

2.5

#### Determination of sample size

2.5.1

Under the hypothesis that with standard method only 42 % of catheter positioning of the NGT allow the measurement of the pH of the gastric aspirate, we want to demonstrate, with a power of 80 % and a type I error of 5 % that the 3 studied NGT allow measurement of pH in at least 62 % of positioning. Therefore, the study need 47 patients in each arm. These numbers were gathered from the current data available at IRCCS Humanitas Research Hospital. This sample size also allows us to see a difference in discomfort between the three study groups as the difference in NGT calibre could be tolerated differently (NRS scale). Following this analysis, a total of 150 patients, subdivided into 50 patients per branch, have to be included in the study.

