#### Statistical analysis

2.5.3

Continuous variables following a symmetric distribution will be presented with mean (SD), while skewed variables will be presented with median (IQR). Ordinal variables will be presented with median (IQR) and categorical variables will be presented as n (%). For primary endpoint, the percentage of catheter positioning allowing pH measurement will also be described with 95 % confidence interval. Differences among the three groups will be explored with chi square test for categorical variables, or one-way ANOVA or Kruskal Wallis test, for continuous variable, depending on their distribution shape. MP patients will also be analysed in order to explore the existence of a different pH threshold to identify the correct catheter positioning in case of use of antiacids-PPIs drugs. All analysis will be performed with Stata version 17 or superior. Statistical significance was set to p < 0.05.

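### The 80% power in section 2.5.1 holds for each tube separately against 42%; it does not hold for all three tubes together, nor for showing a rate of at least 62%

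*Protocol article*

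**What the plan says.** Section 2.5.1 (Determination of sample size) starts from the premise that "with standard method only 42 % of catheter positioning of the NGT allow the measurement of the pH of the gastric aspirate". The Introduction gives the same figure as local experience: "the percentage of patients in whom it was possible to successfully apply this protocol was 42% of all placements performed".

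The aim, set at 80% power and a 5% type I error, is stated as showing "that the 3 studied NGT allow measurement of pH in at least 62 % of positioning". The section then concludes: "Therefore, the study need 47 patients in each arm". This is raised to 50 per arm, 150 in total.

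The section does not name the test or its sidedness. It does not say whether the 80% is for each tube or for the three together.

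Section 2.5.3 (Statistical analysis) reports the primary percentage with a 95% confidence interval, explores differences among the arms with a chi-square test, and adds "Statistical significance was set to p < 0.05". It gives no reference value for reading the interval.

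**The concern.** The sentence that carries the 80% differs from the calculation behind it in two ways.

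- **Subject.** The claim is about the three tubes, while the calculation is about one.
- **Threshold.** The claim is that the rate is at least 62%. In the calculation 62% is the assumed true rate, and the value to be excluded is 42%.

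A reader who takes the sentence at its word would expect an 80% chance of a positive result for all three tubes, when the chance is nearer one half. The same reader could also take an observed 62% as proof of at least 62%. Because section 2.5.3 names no reference value, 62% is the only target in the article against which the result might be judged.

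**Working it through.** **Inputs.** From section 2.5.1: reference rate p0 = 0.42, target rate p1 = 0.62, power 0.80, type I error 0.05, 47 per arm calculated and 50 planned. Two-sided testing is an assumption, made because it reproduces 47; a one-sided test gives 37.2, that is 38.

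**1. Reproducing 47.** One-sample test of a proportion against a fixed p0, normal approximation:

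n = [(z₀.₉₇₅·√(p0(1−p0)) + z₀.₈₀·√(p1(1−p1))) / (p1−p0)]²

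= [(1.960 × 0.4936 + 0.842 × 0.4854) / 0.20]² = (1.376 / 0.20)² = 47.3

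Using the variance at p1 only gives 46.2, which rounds up to 47. The stated figure is therefore a per-arm, one-sample size against a fixed 42%. Comparing two arms at 42% and 62% would need 97 per arm, so that is not what was calculated.

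**2. Power for one tube against 42%, true rate 62%.**

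| n per arm | Test | Cut-off | Power |
|---|---|---|---|
| 47 | normal approximation | – | 79.7% |
| 47 | exact binomial (2.5% upper tail) | 27/47 | 78.7% |
| 50 | normal approximation | – | 82.1% |
| 50 | exact binomial (2.5% upper tail) | 29/50 | 76.8% |
| 50 | score test | 28/50 | 84.6% |

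The stated 80% is delivered per tube. The spread at 50 reflects the choice of test and the discreteness of the binomial.

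**3. Power for all three tubes against 42%.** The arms are independent and each is compared with the same fixed 42%, so the joint power is the per-tube power cubed:

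- n = 47: 0.797³ = 0.51 (normal); 0.787³ = 0.49 (exact).
- n = 50: 0.821³ = 0.55 (normal); 0.768³ = 0.45 (exact); 0.846³ = 0.61 (score).

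A joint power of 80% needs a per-tube power of 0.80^(1/3) = 0.928. That is about 71 per arm by the normal approximation (70.4, rounded up) or 72 by the exact test.

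**4. Showing at least 62%.** An observed 31/50 is exactly 62%. Its exact 95% confidence interval is 47% to 75%, which excludes 42% but includes many values below 62%. For the exact lower limit to lie above 62%, a tube would need 37/47 (79%) or 39/50 (78%).

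**The case against.** The best defence is that the calculation is correct and only the phrasing is loose. Section 2.5.1 opens with 42% as the reference, gives the size for each arm, and nowhere says that success requires all three tubes. Read that way, the 80% is a per-tube figure and it reproduces. This part stands. A reader might infer from the wording that 47 is an arithmetic slip or that the per-tube power is wrong; step 2 shows otherwise.

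A reader might also infer that the trial has only about 1% power, since a lower limit above 62% at a true rate of 62% has probability 1.1% (n = 47) or 1.2% (n = 50) for one tube. That reading is not supported. It uses 62% both as the bound to be excluded and as the truth, so the result is the size of a test, at most 2.5% whatever the sample size. It shows that the sentence names the wrong hypothesis and says nothing against 47.

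The joint figures also depend on each tube sitting at exactly 62%. With 50 per arm and the exact cut-off of 29, the joint power is 61% if every true rate is 64%, 75% at 66% and 86% at 68%. That is a fair qualification, but the stated power is calculated at 62%, so the joint figure belongs at 62% too.

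Finally, multiplicity control for an any-tube claim, and allowance for sampling error in the 42%, are conditional or may be settled in an analysis plan that is not shown. They are not part of this point. What does remain is a stated power attached to a stated objective in the protocol itself, and an analysis plan cannot change which claim 47 per arm was sized for.

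**Conclusion.** The point holds as a mismatch between the stated claim and the calculation, not as a miscalculation. The 80% applies to one tube exceeding a fixed 42%. For all three tubes together the power is about 49–51% at 47 per arm and about 45–61% at the planned 50. The design cannot establish a rate of at least 62% when the true rate is 62%.

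These figures assume a two-sided 5% test, independent arms, a true rate of 62% for every tube, and 42% taken as known without error. Whether the joint figure matters depends on whether a claim for all three tubes is intended. The wording permits that reading and the article does not rule it out.

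**What to change.** Reword the objective in section 2.5.1 along these lines: to show, for each tube separately, that the proportion of placements allowing pH measurement exceeds 42%, assuming a true rate of 62%. In the same section:

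- name the one-sample, two-sided 5% test against 42%;
- say that the 80% is per tube;
- give the joint power for all three tubes (about 50%; 45–61% at 50 per arm, depending on the test);
- state that success for a tube is judged by the lower limit of its 95% confidence interval against 42%, not by whether the observed rate reaches 62%.

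This takes a few sentences and no more patients. The only cost is that the joint power, once stated, is less favourable than 80%. If a joint claim at 80% power were wanted, about 71–72 per arm would be needed, but the rewording does not require that.
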